## Abstract

In every surgical subspecialty surgical site infection (SSI) or implant infections, although occur seldom, pose a threat to patients’ health. Risk factors of such states is diabetes mellitus (DM), considered one of the most widespread health-related problems of the 21st century. Orthopedists perform big joint replacements that usually concern older adults and therefore often deal with patients suffering from comorbidities. DM is frequently one of them and can furthermore often remain underdiagnosed. The other risk for complication is a rapid beginning of the rehabilitation which starts on the day following the surgery. To eliminate the debilitating impact of DM and hypoglycemia on surgical patients, we aim to investigate the relationship between the glycemia values and the postoperative outcomes in certain periods of time in patients undergoing orthopedic surgeries. Participants meeting inclusion criteria will have inserted a glycemia measuring device (Dexcom G5, Inc., San Diego, CA) in the periods of time. First time it will take place 14 days prior to the surgery and right after the surgery for the second time for the period of another 14 days. All patients will undergo standard total knee arthroplasty or total hip arthroplasty procedures. Patients will be assessed preoperatively and 14 days, 1, 3, 6, 12, and 24 months postoperatively. The assessment of the joint condition will consist of: patient-reported outcomes (The Knee injury and Osteoarthritis Outcome Score, Harris Hip Score, the Western Ontario and McMaster Universities Osteoarthritis Index [WOMAC]); assessment of potential SSI and cardiovascular complications (the Finnish Diabetes Risk Score [FINDRISC], the Systematic Coronary Risk Evaluation [SCORE]) and the clinical examination. To investigate the influence of orthopedic surgery (anesthesia) on glycemia and the significance and safety of early patients mobilization after the big joints surgeries. To investigate changes of glycemia in patients with normal glycemia metabolism, potentially protecting them from hypoglycemia during hospital stay and increasing their awareness of potential development of DM in the future. Additionally, this study will correlate perioperative glycemic levels with risk of cardiovascular events in one year follow-up, and its influence on SSI and implant complications.

## 1. Introduction

In every surgical subspecialty surgical site infection (SSI), although occur seldom, pose a serious threat to a patients’ health.^[1,2]^ Among the most known risk factors of such states are glucose metabolism disorders, which including diabetes mellitus (DM), are considered one of the most widespread health-related problems of the 21st century.^[3,4]^ DM is a civilization disease, expected to reach almost 600 million people by 2030^[5,6]^ Hyperglycemia is a potentially reducible risk factor for a variety of complications after a surgical procedure, including infections.^[7]^ Both the World Health Organization and U.S. Centers for Disease Control and Prevention recommend perioperative glucose control,^[8,9]^ but there is debate over which surgical patients should be treated and what protocol would maximize benefits and eliminate side effects. Recently, a stronger link between postoperative hyperglycemia and adverse outcomes in patients without diabetes than in patients with diabetes has become evident, suggesting that patients without diabetes may benefit especially from glucose control.^[10]^ Many patients undergoing orthopedic surgery may have unrecognized diabetes or may develop stress-related hyperglycemia in the hospital. The challenge is to minimize the effects of metabolic derangements on surgical outcomes, reduce glycemic excursions, and prevent hypoglycemia.^[11–13]^ There are no clear guidelines advocating evidence-based glucose targets in the inpatient setting and regimens. Individualized treatment should be based on the ambient level of glycemic control, outpatient treatment regimen, presence of complications, nature of the surgical procedure, and type of anesthesia administered. Management by a multidisciplinary team and attention to discharge planning are key aspects of care during and after orthopedic surgery.^[14–16]^

For critically ill patients, the American Association of Clinical Endocrinologists and the American Diabetes Association have recommended revising glucose targets precisely. In patients who are not critically ill, the recommendations are based on clinical experience and judgment. Hence, a reasonable general target for the hospitalized orthopedic patient undergoing surgery is 110 to 180 mg/dL. These goals should be flexible and individualized to the particular patient and the clinical circumstances, which sometimes can be difficult to conclude.^[15]^

The available data focus on increased risk for experience of complications or adverse events by patients with DM. However, there is a lack of literature containing analysis of continuous glycemia measurements before and after hospitalization. There are some reports that glycemic variability during postoperative period might also increase the risk of cardiovascular events or lead to more frequent periods of hypoglycemia, which might result in higher risk of losses of consciousness and falls, higher cardiovascular risk, disability, and mortality.^[16–23]^ However, few studies have reported on the effect of hypoglycemia during the perioperative period.^[24]^ Taking into consideration, that median length of hospital stay after TKA and THA is 3 days, the rehabilitation beginning on the day following the surgery may interfere with hypoglycemia or orthostatic hypotension. Patients at whom glycemia is not well controlled and despite are forced to perform rehabilitation program may develop debilitating consequences.

With the prevalence of this disease predicted to continue to increase and TKA, and THA being among the most common surgeries, it is important for orthopedic surgeons to consider glycemia in their plan of risk reduction for adverse postoperative events. If we consider the common risk factors of DM and OA, such as obesity, it seems that the number of patients having both diseases is threateningly big. According to the aforementioned literature, it is clear that the appropriate screening must be performed routinely. Depending on the results, administration of medications intra- and postoperatively has been shown to improve clinical outcomes. Individual patient characteristics and surgical case factors would be considered to choose the therapy. But to approach the patients with the individualized treatment modality, we must previously investigate the association of altered glucose status among them, thus based on the clinical studies. This factor remains the major rationale of the presenting study.

## 2. Materials and Methods

Patients for this prospective observational study will be recruited among those qualified for elective TKA or THA at the Department of Orthopaedics and Rehabilitation in academic Miedzyleski Specialist Hospital in Warsaw. 100 patients will be included. Every patient will be evaluated with the use of Finnish Diabetes Risk Score (FINDRISC), which allows for evaluation of risk of developing DM in 10 year time in patients who were not previously diagnosed^[25–27]^ and SCORE scale, which allows for evaluation of risk of death in 10 years due to cardiovascular events.^[28–31]^ To perform this evaluation data such as sex, age, body mass index (kg/m^2^), and waist circumference (cm) will be measured. Also, data such as physical activity, diet, used medications, smoking, and family history will be collected. Prior to the surgery every patient will undergo a blood withdrawal, which is routinely performed for every patient qualified for the orthopedic surgery. This blood sample analysis will include glycemia level, HbA1c, morphology, renal function parameters, lipidogram, level of C-reactive protein, and urine test. What is more, every patient will fulfill a questionnaire regarding functioning of the joint affected by OA. The scales used will be The Knee injury and Osteoarthritis Outcome Score scale (Knee injury and Osteoarthritis Outcome Score)^[32]^ or Harris Hip Score (HHS) scale^[33]^ according to the affected joint. Both scales contain questions about patients’ everyday life and limb function.

Inclusion criteria consist of willingness to participate in the study, being qualified for TKA or THA due to the primary OA and age >18 years.

Exclusion criteria consist of lack of acceptance to participate in the study, being qualified for nonsurgical treatment, other diseases but DM, compensated thyroid disorders and hypertension, poorly controlled DM and/or poorly controlled hypertension, patients with diabetes mellitus type 1, patients from the rest homes, pregnant women, patients who underwent lower limb surgeries recently, patients who in opinion of the research team might be poorly compliant, poor Polish language fluency.

Patients will have a glycemia measuring device (Dexcom G5, Inc., San Diego, CA) implemented twice. First time 14 days prior to the surgery, second time after the surgery and will keep wearing it for 14 days.

All patients will undergo TKA and THA procedures with standard perioperative antibiotics prophylaxis with use of 3 doses of 750 mg of cefuroxime–preoperatively, 6 and 12 hours postoperatively, and standard thrombosis prophylaxis of one dose of 40 mg low-molecular weight heparin. In every case posterior-stabilized total knee prosthesis (PERSONA, Zimmer Biomet, Warsaw, IN) or long-stem cementless Polarstem R3 total hip prosthesis (Smith & Nephew, Baar, Switzerland) will be used. Every participant will be rehabilitated immediately after the surgery with full weight bearing walking in the first 24 hours postoperatively, with the discharge from the hospital on the third day postoperatively.

During standard control visit, 14 days after the surgery skin sutures will be removed and the glycemia measuring device will be taken out. The measurements from the whole period of treatment will be collected from the device. Patients will be controlled during the planned visits 3, 6, 12, and 24 months after the surgery. In case of hyperglycemic event at any time of hospital stay or follow-up, patients will be referred to the internal medicine unit and remain controlled by the physicians according to the glycemic control guidelines.

During every visit glycemia level will be measured from standard blood samples, objective functional outcome will be assessed and radiological standard imaging of the operated limb will be performed. History of any cardiovascular event and/or surgical SSI will be noted.

The presenting study meets STrengthening the Reporting of OBservational studies in Epidemiology guidelines for ensuring high-quality presentation of the conducted prospective observational study.

## 3. Ethics, data management, and statistical analysis

All procedures used for this study have been approved by the Institutional Bioethics Committee of the Medical University of Warsaw (number of approval: KB/104/2020). The study was registered in the ClinicalTrials.gov database (NCT04484480). All patients will be obliged to give written consent for their participation in the study. Collected data will be stored at the Department in a database created particularly for this study and secured appropriately. In the database each participant will have a special code to minimize the risk of identification of a particular patient. Only patients who attend all visits, fill in all questionnaires and do not interrupt the course of the study in any other way will be included in the analysis. The consequence of the absence on a control visit will be exclusion from the study.

Power analysis was performed to assess how many patients should be included in the study. Determining effect size was hindered by lack of literature comparing mean values and standard deviations (SD) between groups with and without complications. The effect size can be deemed “large,” described numerically as 0.8 by Cohen. However, we decided to be more conservative and used an effect size of 0.6, located between “medium” and “large” in Cohen scale. Standard *P* value of .05, beta value of 0.8, and allocation ratio of 1/1 were used, resulting in a total needed sample size of 90 patients. Taking into consideration that 10% of patients might drop off the follow-up predicted number of participants is 100.

Basic analysis will include descriptive statistics of demographic characteristics to assess both groups homogeneity. Such analysis will be done several times during testing to detect any confounders that could impact the results. Continuous variables will be summarized with number of cases, means, standard deviations, medians, ranges, and first and third quartile (Q1 and Q3). All comparisons will be performed between continuous variables in paired groups, therefore either a 2-sided Student *t* test for paired groups or Wilcoxon Signed Rank test will be used. Distribution normality will be examined using the Shapiro–Wilk test. An overall alpha-level of 0.05 will be used as a cut-point for statistical significance and all statistical tests will be 2-sided. Significance level will be set at *P* value below .05. Outliers will be initially identified using interquartile range (IQR) as observations with values above Q3-1.5IQR or below Q1-1.5IQR and will be examined individually. All data will be presented with extreme and outlier observations or committed with appropriate annotation.

All statistical analyses will be conducted using SAS 9.4 for Windows (SAS Institute Inc., NC).

The study protocol was published before the start of the study on clinicaltrials.gov. The results of the study will be published in (inter-)national scientific journals and guidelines. The data that support the findings of this study will be available from the corresponding author - OA, upon reasonable request.

Data reported in the presenting study will be prospective observational data. The treatment will be reliable to the patients’ condition. And the procedure of implementing the glucose measuring device will be the same throughout the whole cohort. This has to be kept in mind for the interpretation of the results.

The inclusion and exclusion criteria presize how the authors deal with the risk of bias such as severity of illness or presence of comorbidities on intervention group assignment.

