## 4. Outcomes measure

### 4.1. Primary outcomes

Changes of glycemia levels during 4-week perioperative period: mean glucose level during pre- and postoperative period, 24-hour glucose level amplitude, time of both higher and lower glucose level than average for the day in total, number of periods of both higher and lower than average glycemia levels for the day and its’ duration, number of days with higher mean glucose level than the mean for the corresponding pre- and postoperative period;Any cardiovascular events during follow-up (heart stroke, brain stroke, coronary arteries disease, transient ischemic attack;Any surgical site and/or implant complications during follow-up.

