Results of the presenting paper will allow us to investigate the influence of orthopedic surgery on glycemia and possible modifications of hyperglycemia treatment in perioperative period in patients with T2DM or glucose intolerance. What is more, it will allow for investigation of changes of glycemia in patients with normal glycemia metabolism, potentially protecting them from hypoglycemia during hospital stay and increasing their awareness of potential development of DM in the future. Additionally, this study will correlate perioperative glycemic levels with risk of cardiovascular events in 1-year follow-up, and its influence on SSI and implant complications. Thanks to these findings surgeons will be able to lower the risk of such complications in the future, hence lowering mortality and increase the quality of life, especially in patients with DM and in those with high risk for developing this disorder. Another advantage of this study is the fact that it contains patients without recognized DM and without carbohydrate metabolism disorders and assesses their glycemia fluctuations. Such knowledge might help in development of an algorithm for perioperative care with stress on glucose level control as it is a period when patients are exposed to significant glycemia fluctuations. What is more, it must be emphasized that this study has a unique model, in which glycemia monitoring will involve both pre- and postoperative period for every included patient. Such a way of analyzing patients allows one to form a well visualizing control group, because every measurement after the surgery has its counterpart before the surgery. However this study did not exclude the disadvantages. Patients before the surgery and after hospital discharge will not be monitored all the time. Therefore, we must take into consideration the possible patients’ interference with glycemia levels in opposition to recommendations. That may lead to obtaining invalid results and risk of bias.

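### Membership of the analysis set depends on complete attendance to 24 months, which removes every patient who dies before the last visit, may bias the primary event outcomes, and discards glucose data already complete at day 14

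*Protocol article*

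**What the plan says.** The rule is in the protocol article, section 3 (Ethics, data management, and statistical analysis). The analysis is open to these patients alone: "Only patients who attend all visits, fill in all questionnaires and do not interrupt the course of the study". The next sentence reads: "The consequence of the absence on a control visit will be exclusion from the study". No exception is made for death, readmission or revision surgery, and no separate set is named for any outcome.

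Section 4.1 lists three primary outcomes. The first is the change in glycaemia over the four perioperative weeks. The others are "Any cardiovascular events during follow-up" and "Any surgical site and/or implant complications during follow-up".

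The Methods (section 2) place sensor removal and data collection at the 14-day visit, and then state: "Patients will be controlled during the planned visits 3, 6, 12, and 24 months after the surgery". The history of cardiovascular events and surgical site infection is noted at visits; no other source is described. The Abstract gives a longer visit list: "Patients will be assessed preoperatively and 14 days, 1, 3, 6, 12, and 24 months postoperatively". The Discussion sets a shorter horizon for one aim, to "correlate perioperative glycemic levels with risk of cardiovascular events in 1-year follow-up".

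Section 3 allows for 10% loss, which takes 90 patients to 100.

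**The concern.** Entry to the analysis is decided by what happens after surgery, over up to two years. Cardiovascular events and surgical site or implant complications are primary outcomes, and they can themselves prevent a patient from meeting the entry condition.

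- **Deaths.** A patient who dies before the 24-month visit cannot attend all visits. A fatal infarction or stroke leaves both numerator and denominator, and so does any infection or non-fatal event recorded earlier in that patient.
- **Non-fatal events.** These patients drop out only if they miss a visit, leave a questionnaire unfilled or otherwise interrupt the study.
- **Association with glycaemia.** The Introduction and Discussion link disturbed glycaemia to falls and mortality. If those links hold, exposure and outcome both influence who is analysed. The glycaemia-complication association can then be distorted, not merely less precise.
- **Glucose outcome.** It is complete at day 14, yet is thrown away for a visit or questionnaire missed months later. The document gives no reason for this.

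Because the rule is stated outright, it is not a detail left to an analysis plan.

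**Working it through.** **1. The plan's own figure.** Inputs from sections 3: effect size 0.6, two-sided alpha 0.05, power 0.8 (printed as beta), ratio 1:1. A two-sample t-test needs 44.59 per group, so 45 per group and 90 in total. With 10% loss, 90 / 0.90 = 100. Both stated figures reproduce; the arithmetic is not at fault.

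**2. What the 10% allowance requires under the all-visits rule.** Let p be attendance per visit and k the number of postoperative visits. If misses are independent, the fraction who attend everything is p^k. The Methods give k = 5 (14 days; 3, 6, 12 and 24 months). The Abstract adds a 1-month visit, so k = 6.

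- To keep 90%: p = 0.9^(1/5) = 0.979, or 0.9^(1/6) = 0.983.
- At an assumed p = 0.95: 0.95^5 = 0.774 and 0.95^6 = 0.735, that is about 77 or 74 of 100 patients.

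Unfilled questionnaires would come on top. If the losses are instead permanent dropouts, so that the same patients miss all later visits, 10% loss by 24 months leaves exactly 90.

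**3. Event risk seen among completers.** Let r be the true risk, c1 the completion rate of patients with an event and c0 that of patients without one.

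Observed risk = r·c1 / [r·c1 + (1 − r)·c0]

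The document gives none of these three. Assume r = 0.05 and c0 = 0.90, so that (1 − r)·c0 = 0.855.

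| c1 | Calculation | Observed risk |
|---|---|---|
| 100% | 0.0500 / 0.9050 | 5.5% |
| 90% | 0.0450 / 0.9000 | 5.0% |
| 70% | 0.0350 / 0.8900 | 3.9% |
| 50% | 0.0250 / 0.8800 | 2.8% |
| 25% | 0.0125 / 0.8675 | 1.4% |

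For events fatal before the last visit, c1 = 0 by definition and the observed risk is 0.

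**4. How few events there may be.** The only cardiac rate in the document is 0.2% to 0.8% for major cardiac complications (Discussion). In 100 patients that is 100 × 0.002 = 0.2 to 100 × 0.008 = 0.8 expected events. At such counts, excluding one patient with an event can empty that component.

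**5. Power for the glucose comparison.** Section 3 makes the comparisons paired. If 0.6 is read as the paired standardised effect (an assumption), a two-sided paired t-test needs 24 patients for 80% power. With 74 patients its power exceeds 0.99. At an assumed effect of 0.35, power is 0.84 with 74 patients against 0.91 with 90.

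**The case against.** The strongest reply is that the rule removes less than it first seems to.

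- **Non-fatal events.** A reader might infer that all patients with serious complications are removed. The text does not say so. Event history is noted at each visit, so a patient with a stroke, infection or revision who attends and completes everything is counted. This stands.
- **Direction.** A reader might also infer that event rates must be too low. Nothing in the document shows that complications reduce attendance, and patients with wound or implant problems may stay in closer contact with the department. If all of them completed, the observed risk would be 5.5% against a true 5%. This stands too: a downward error is certain only for fatal events.
- **Loss allowance.** It is tempting to call 10% impossible under this rule. It holds at about 98% attendance per visit or under permanent dropout, and section 2 excludes patients expected to comply poorly. Optimistic is the right word.
- **Power.** A serious loss of power for the paired glucose comparison is not supported. Selection and needless waste of data are the issue there.
- **Rare events.** If cardiac events are as rare as cited, repairing the rule will not make them informative. That is true, but it is no reason to drop those that occur.

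None of these replies justifies excluding patients who die, or setting aside glucose data that are already complete.

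**Conclusion.** The rule is wrong as written and should be replaced before analysis. Three consequences follow from the text without any assumption: every patient who dies before the last visit leaves the analysis, any earlier event in that patient leaves with them, and glucose data complete at day 14 are lost for a later absence.

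Beyond that, the primary event rates and the glycaemia-complication association may be biased. Underestimation of events is probable, but its size cannot be derived from the document. The range of 5.5% down to 1.4% around a true 5% rests on an assumed risk and assumed completion rates. The attrition figures of about 77 or 74 patients assume 95% attendance per visit and independent misses. Enrolling 100 instead of 90 restores numbers; it does not remove selection.

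The differing visit lists and event horizons are a separate drafting matter. A one-year correlation within 24 months of follow-up is not strictly a contradiction. Under an all-visits rule, however, whether the 1-month visit exists changes who is analysed.

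**What to change.** Replace both sentences in section 3 with an analysis set for each outcome.

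- **Glucose:** all operated patients with usable pre- and postoperative sensor data, regardless of later attendance.
- **Events:** all operated patients, with cardiovascular, surgical site and implant events counted up to death or last contact within one stated horizon. Fatal cardiovascular events are counted and other deaths accounted for. When a visit is missed, status is taken from hospital records or by telephone.
- **Functional scores:** available data from every patient; the choice of model can be left to the analysis plan.
- **Complete attenders:** kept only as a sensitivity analysis.

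Separately, reconcile the 1-month visit (Abstract against section 2) and the event horizon: one year in the Abstract and Discussion, and unspecified follow-up in section 4.1 with visits to 24 months.

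The cost is revised wording and a few record checks or calls. No extra patients or visits are needed.

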## 6. Discussion

It is well established that DM in patients undergoing surgery is associated with increased risk for complications and increased length of hospital stay.^[45]^ In general, hyperglycemia is considered to cause abnormalities in the host’s physiologic response to a bacterial load not only in diagnosed with DM patients.^[46]^ Fasting blood glucose of > 140 mg/dL has been associated with a 3-fold increased risk for an infection independently on glucose metabolism.^[47]^

Periprosthetic joint infection remains a devastating complication after THA. Poor patient satisfaction and increased socioeconomic costs are associated with this along with increased mortality.^[48–50]^

Total joint arthroplasty is considered a relatively safe procedure globally for an overall condition, as reported rates of major cardiac complication, mostly attributable to myocardial infarction, are as low as 0.2% to 0.8%.^[51,52]^ However, this risk is prognosed to increase significantly with the predicted increase in number of arthroplasties in the future, therefore the adequate measures to minimize the influence on body metabolism, must be developed.^[53–55]^ Factors associated with cardiac complications are increased hospital mortality, increased length of stay and expenditure, increased number of noncardiac events.^[53,56–60]^

The literature lacks valuable information indisputably designing an evidence-based approach to patients suffering from T2DM in orthopedic surgery departments to decrease prevalence of potentially debilitating adverse events. Since there are currently available only empiric recommendations, there is a need for well-designed studies of preoperative T2DM management, particularly for orthopedic surgeries. This could minimize procedure delays, patients’ dissatisfaction and reduce morbidity and mortality. Hyperglycemia on the day of surgery is a significantly dangerous circumstance for both nondiabetic and T2DM patients, thus there is an urgency of developing the guidelines of proceeding on the patients presenting with this condition.^[61–63]^ The up-to-date database search utilized only a few papers investigating the role of preoperative glycemia on the postoperative outcomes.

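### The sample size of 90 assumes half the cohort will have complications, which the protocol's own event rates make untenable, and it does not match the paired analysis

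*Protocol article*

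**What the plan says.** Section 3 of the Protocol article says the choice of effect size was hampered by "lack of literature comparing mean values and standard deviations (SD) between groups with and without complications". The authors therefore "used an effect size of 0.6, located between “medium” and “large” in Cohen scale". With a P value of .05, "beta value of 0.8, and allocation ratio of 1/1 were used, resulting in a total needed sample size of 90 patients". An allowance of 10% for dropout raises this to 100.

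The same section then sets out the analysis: "All comparisons will be performed between continuous variables in paired groups", by paired t test or Wilcoxon signed rank test. "An overall alpha-level of 0.05 will be used as a cut-point for statistical significance", and "all statistical tests will be 2-sided". Section 6 explains the pairing: each patient's postoperative measurements are set against that patient's own preoperative ones.

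On event frequency, the abstract and introduction describe surgical site infection as infrequent (the abstract adds implant infection). Section 6 states that "reported rates of major cardiac complication, mostly attributable to myocardial infarction, are as low as 0.2% to 0.8" per cent. Section 4.1 lists cardiovascular events and surgical site or implant complications among the primary outcomes, next to the glycaemia changes.

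**The concern.** An allocation ratio belongs to a comparison of two separate groups. The only two groups named in the power paragraph are patients with and without complications. Nobody is allocated to having a complication. The study is one prospective observational cohort, and no case-control sampling or matching is described, so the split will be whatever the event rate makes it. A 1:1 split means 45 of 90 patients with a complication, which conflicts with the article's own account of how rare these events are.

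The tests that are named do not compare those groups at all. The one power statement in the article therefore covers a comparison that the cohort cannot deliver in that form and that the analysis text does not contain.

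What is at stake is the reading of a null result. The abstract and discussion promise to relate perioperative glycaemia to cardiovascular events and to surgical site and implant complications. If no association is found, the article's 80% power will appear to support a conclusion of no association.

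**Working it through.** **Inputs from the article.** d = 0.6; two-sided alpha 0.05; ratio 1:1; dropout 10%; major cardiac complication rate 0.2% to 0.8%; all planned tests paired. **Assumption.** The article gives no rate for complications overall, so a range of 2% to 40% is used.

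**1. Reproducing 90 and 100.** For an unpaired t test the noncentrality parameter is d × √(n₁n₂/(n₁+n₂)).
- 45 and 45: 0.6 × √22.5 = 2.85, power 80.4%.
- 44 and 44: power 79.5%.

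So 45 per group, 90 in total, is the smallest size that reaches 80%. Dropout: 90 / (1 − 0.10) = 100. Both figures reproduce. A one-sided test would need 36 per group (72), which does not match.

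**2. The label on 0.8.** The article writes "beta value of 0.8, and allocation ratio of 1/1 were used". If beta were 0.8, power would be 0.2, and 8 per group would be enough (power 20.1%). Only power 0.8, that is beta 0.2, leads to 90.

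**3. Power for the complication comparison, 90 analysed, d = 0.6, by number of patients with a complication.**

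| With / without | Noncentrality | Power | d detectable with 80% power |
|---|---|---|---|
| 2 / 88 | 0.84 | 13% | 2.03 |
| 4 / 86 | 1.17 | 21% | 1.45 |
| 9 / 81 | 1.71 | 39% | 1.00 |
| 18 / 72 | 2.28 | 62% | 0.75 |
| 45 / 45 | 2.85 | 80% | 0.60 |

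**4. Power averaged over the chance number of events.** The event count is Binomial(90, r), and samples with no event count as zero power.

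| Assumed rate r | Expected events | Average power |
|---|---|---|
| 2% | 1.8 | 12% |
| 5% | 4.5 | 23% |
| 10% | 9 | 39% |
| 20% | 18 | 61% |
| 30% | 27 | 73% |
| 40% | 36 | 78% |

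Even at 20%, the chance of 45 or more events among 90 patients is about 2 × 10⁻¹⁰.

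**5. The article's own cardiac rate.**
- At 0.2%: 90 × 0.002 = 0.18 expected events; chance of none 0.998⁹⁰ = 84%.
- At 0.8%: 90 × 0.008 = 0.72 expected events; chance of none 0.992⁹⁰ = 49%.

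**6. The comparison actually planned.** For a paired t test the noncentrality parameter is dz × √n, where dz is the mean change divided by the SD of the within-patient differences.
- dz = 0.6: 24 pairs give 80.4% power; 90 pairs give more than 99.9%.
- 90 pairs: 80% power at dz of about 0.30 (0.30 × √90 = 2.85).
- If 0.6 is instead measured in units of the between-patient SD, dz = 0.6 / √(2(1 − ρ)). At a before/after correlation ρ of 0 this is 0.42, and 90 pairs give 97.8% power. Power is higher for any positive correlation.

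**The case against.** The arithmetic is not at fault: 90 and 100 are both right for the design assumed, and the intended meaning of the 0.8 is clear. This stands. The fault is in the premise and in the mismatch with the planned test.

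The 0.2% to 0.8% covers major cardiac complications only. The event outcomes in section 4.1 are wider, including coronary disease, transient ischaemic attack and any surgical site or implant complication, with visits to 24 months. Their combined rate is not given and could be well above 1%. This also stands, and it is why a range is shown. It does not rescue the 80%: average power is 61% at a rate of 20% and is still below 80% at 40%.

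The sentence with the ratio does not itself name the groups. The link to complication status comes from the sentence on the missing literature just before it. No other pair of independent groups is defined there, however, and a paired calculation has no allocation ratio and would not give 90.

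For the glycaemia changes tested as planned, the study has more than enough patients. That is correct: the mismatch there is an excess, and the shortage is confined to the complication comparison. A test for that comparison may appear in a fuller plan, but an 80% claim based on a 1:1 split would be just as untenable there.

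Finally, a detectable difference of 0.30 SD is worked back from the number of patients and does not show that such a change matters. This is fair, and the restated text should present it as what the sample can detect.

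**Conclusion.** The concern holds. The 90 is the size of an unpaired 1:1 comparison of patients with and without complications, and that split would need 45 complications among 90 patients. At assumed complication rates of 2% to 20%, the power for d = 0.6 is about 12% to 61%. With 9 events, only a difference of about 1.0 SD is detectable with 80% power; with 4 events, about 1.45 SD. For major cardiac events at the article's own rates, there is a 49% to 84% chance of seeing none.

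The paired before/after comparison is well powered, so enrolment is not in question. What must be corrected is the justification and the power claim attached to the complication outcomes.

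The result assumes that 90 patients are analysed and that the 1:1 ratio refers to complication status. The 2% to 40% rates are assumptions, but no plausible choice among them restores the stated power.

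**What to change.** Keep the target of 100 and replace the justification in section 3 along these lines:

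- **Power statement.** With 90 evaluable pairs, the study has 80% power (beta 0.20, two-sided alpha 0.05) to detect a change in mean glucose from before to after surgery of 0.30 SD of the within-patient differences. Present this as the detectable change.
- **Remove** the power claim for patients with versus without complications, together with the 1:1 allocation ratio.
- **Event outcomes.** Keep them as outcomes and report them as proportions with exact 95% confidence intervals. For scale, zero events in 90 gives an upper limit of 1 − 0.025^(1/90) = 4.0%.
- **Glycaemia–event associations.** Describe them as exploratory, and align the abstract and discussion with that.
- **Label.** Change the beta of 0.8 to power of 0.8.

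The cost is wording only, with no change in enrolment, visits or data collection. The article gives up a claim of 80% power for complications that the design does not support.
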